aged 65 years or older and residing in an LTC facility;no mild or moderate frailty (i.e., Clinical Frailty Scale: level < 5), according to Rockwood [14] (as assessed by caring professionals);able to give informed consent (as assessed by caregivers and, if applicable, legal guardians); andsufficiently able to hear (i.e., 80% speech comprehension at an everyday speech volume).

The exclusion criteria will be as follows:

a current diagnosis of a swallowing, speech, and/or language disorder and an associated prescription for speech, swallowing, or language therapy;suspected aspiration (i.e., EAT-10 score > 2);moderate or severe dementia (i.e., DemTect ≤ 8); andestimated life expectancy of < 6 months, based on the “Double Surprise Question” (as assessed by caring professionals) [15].

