### Data collection

#### Sample size calculation

The primary outcome variable will be swallowing capacity, as measured via the Timed Test of Swallowing Capacity (TTSC). Based on a two-tailed unpaired t-test with a significance level set to 5% and a power of 80%, *n* = 5 clusters per group will be required (assuming *n* = 8 individuals per cluster). Anticipating a difference in the change in swallowing capacity of 2.8 ml/s between groups, with a pooled standard deviation of 3 ml/s [16] and an ICC of 0.1 [14, 15],^1^*n* = 10 clusters with a combined total of *n* = 80 individuals will be required.

Studies investigating individuals with pre-existing dysphagia in nursing homes [16] and nursing home residents, more generally [17], have reported dropout rates between 10 and 52%. According to the defined inclusion and exclusion criteria, the present study will address less vulnerable residents with no pre-existing dysphagia. Thus, a lower dropout rate of approximately 20% is assumed. On the basis of these assumptions, a sample size of approximately *n* = 100 participants in 10–12 clusters (i.e., 5–6 intervention facilities and 5–6 control waiting facilities) will be required.

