#### Data processing and statistics

Data collected in the LTC facilities, test results, and data from the structured surveys will be saved (i.e., input) and analyzed using the Statistical Package for the Social Sciences for Windows (SPSS Inc., Chicago, IL/USA), in the version currently available at the Institute. The data will be stored on the secure servers of Hannover Medical School, and access to the data will be limited to the research team. For quality assurance, random checks of every fifth entry in the test protocols and plausibility checks will be carried out. Given the low risk of the preventive intervention, no external data monitoring committee is deemed necessary.

As part of the process analysis, meeting minutes and free-text answers to the surveys will be transcribed and pseudonymized. The research team are familiar with the recommendations for good scientific practice in qualitative research, with respect to data protection [23]. Any missing values will be replaced sensibly and conservatively.

Statistical significance will be determined by *p*-values < 0.05. Descriptive statistics will be employed to define frailty, hearing, swallowing, speech, cognitive abilities, and changes over time. A descriptive analysis will be conducted regarding the participating LTC facilities, the intervention study population, and the control waiting group. Additionally, a comparative analysis of central characteristics (i.e., gender distribution, age, frailty, etc.) will be carried out.

The primary endpoint will be evaluated at the individual level, according to the intention-to-treat principle. To detect statistically significant differences in the change in TTSC between groups at t_0_, t_1_, and t_2_, an unpaired t-test will be conducted with a two-sided significance level of 5%. Given a *p*-value < 0.05, any difference will be deemed statistically significant.

For the exploratory analysis of the secondary endpoints of language ability, subjective assessment of swallowing ability (according to the EAT-10), and communicative practice (according to the CAL), a comparative analysis will be conducted between the intervention and control waiting groups at t_0_, t_1_, and t_2_, using t-tests for unconnected samples [309]. A separate comparative analysis of the endpoints between measurement time points within the intervention group and the control waiting group will be conducted, using t-tests for connected samples.

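### The exploratory secondary endpoints are compared between arms without using each participant's baseline, and paired tests within each arm do not test the randomised contrast

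*Protocol article*

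**What the plan says.** *Data processing and statistics* in the protocol article fixes three sets of tests and sets p < 0.05 as the threshold for significance.

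- **Primary.** The change in TTSC is compared between arms by an unpaired t-test, with no covariate named.
- **Secondary, between arms.** For language ability, EAT-10 and CAL, labelled exploratory, "a comparative analysis will be conducted between the intervention and control waiting groups at" t0, t1 and t2, by unpaired t-tests. Neither a change score nor the t0 value is mentioned.
- **Within arms.** "A separate comparative analysis of the endpoints between measurement time points within the intervention group and the control waiting group will be conducted", by paired t-tests. Whether *the endpoints* here include TTSC is not clear.

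Table 1 shows TTSC, RWT, CAL and EAT-10 all measured at t0, t1 and t2, so a baseline exists for each. The same section also plans linear and logistic regression to explore associations, with facility and sex as examples. It does not name the t0 score as a covariate and does not make these models the treatment comparison.

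**The concern.** Two weaknesses follow for the secondary endpoints.

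First, a t-test on raw scores at t1 or t2 leaves all stable differences between residents in the error term. It also lets part of any baseline gap between arms pass into the result. With 10 to 12 facilities such gaps can be sizeable. They need not be due to chance alone: *Characterization of LTC facilities as clusters and participants* and Table 1 place facility allocation before resident recruitment and consent.

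Second, separate paired tests ask whether each arm changed, not whether the arms differ. Practice on repeated testing, natural course, or the more critical self-rating at t1 that the article itself anticipates can all move an arm. A pattern of significance in one arm only can then pass for an effect. The main hypothesis is about preventing decline, so the mirror pattern (control declines significantly, intervention does not) is equally tempting.

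The exploratory label limits the damage but does not remove it. The article closes by saying that positive results for swallowing, communication or both are expected to lead to such programmes being offered more widely.

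**Working it through.** **1. The plan's own figure.** Inputs from *Sample size calculation*: "Based on a two-tailed unpaired t-test with a significance level set to 5% and a power of 80"%; "Anticipating a difference in the change in swallowing capacity of 2.8 ml/s between groups"; "with a pooled standard deviation of 3 ml/s"; ICC 0.1; 8 per cluster; dropout about 20%.

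- n per arm = 2 × (1.960 + 0.842)² × 3² / 2.8² = 18.02, rounded up to 19.
- Design effect = 1 + (8 − 1) × 0.1 = 1.7, so 19 × 1.7 = 32.3 per arm; 32.3 / 8 = 4.04, rounded up to 5 facilities per arm, 80 people in all.
- A t-test on facility means (8 df) with 5 per arm has power 0.800.
- 80 / (1 − 0.20) = 100.

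The stated sample size reproduces.

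**2. Within-arm tests when both arms change equally.** Take 40 analysed per arm and a true common improvement of d SDs of the change (d is assumed). Each paired test has noncentrality d√40 on 39 df. With P the chance that one test is significant, the chance that the intervention arm is significant and control is not is close to P(1 − P). The last column is a simulation (40,000 runs, 5 facilities of 8 per arm, ICC 0.1 in the changes, paired tests that ignore facility).

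| d | P | Intervention only | Intervention only, clustered |
|---|---|---|---|
| 0.2 | 0.235 | 18% | 21% |
| 0.3 | 0.457 | 25% | 25% |
| 0.45 | 0.793 | 16% | 19% |

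For an equal decline, control significant and intervention not has the same probability, by symmetry.

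**3. Precision between arms.** With equal variance σ² at each visit and baseline to follow-up correlation ρ (not given in the article; 0.3 to 0.9 assumed), the variance per person is σ² for a raw follow-up score, 2σ²(1 − ρ) for a change score and σ²(1 − ρ²) after baseline adjustment. Hence raw/adjusted = 1/(1 − ρ²) and adjusted/change = (1 + ρ)/2. Power for the primary holds the SD of the change at 3 ml/s, with 5 facilities of 8 per arm and 8 df.

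| ρ | Raw/adjusted variance | Adjusted/change variance | Primary power, adjusted (change score: 0.80) |
|---|---|---|---|
| 0.3 | 1.10 | 0.65 | 0.93 |
| 0.5 | 1.33 | 0.75 | 0.90 |
| 0.7 | 1.96 | 0.85 | 0.86 |
| 0.9 | 5.26 | 0.95 | 0.82 |

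If the covariate costs one cluster-level degree of freedom (7 df), the powers are 0.92, 0.89, 0.84 and 0.80.

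**4. Baseline gaps.** With 6 facilities of 8 per arm and the TTSC ICC of 0.1 borrowed for the other outcomes (an assumption), the SE of a chance gap is √(2 × 1.7 / 48) = 0.27 SD, and a gap above 0.3 SD occurs in about 26% of trials. This ignores the planned stratification, which could lower it, and recruitment after allocation, which could raise it. In expectation ρ times the gap carries into the raw follow-up comparison: for a 0.3 SD gap, 0.09 SD at ρ = 0.3 and 0.27 SD at ρ = 0.9.

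**The case against.** Several stronger readings are tempting, and the article does not support them.

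- **That the baseline is wasted for the primary endpoint, or that its test is invalid on this account.** A change score uses t0, is a valid comparison between arms under randomisation, and is the quantity the sample size was built on. What is lost is efficiency only.
- **That equal change in both arms can pass for benefit throughout the plan, or in half of trials.** Only the paired tests have this fault; the between-arm tests do not. One arm alone is significant in up to about 50% of trials (d = 0.3), but only one direction favours the intervention, which halves the figure.
- **That the plan will claim an effect from discordant within-arm p-values.** It does not say so, and between-arm tests are planned alongside. The weakness is that nothing names one of these as the treatment comparison.
- **That a t0 test can only detect chance.** Residents are recruited after facilities are allocated, so a t0 difference may be systematic and worth seeing. But with 10 to 12 facilities a p-value is a poor guide to whether it matters; its size is more useful.
- **That the EAT-10 entry limit manufactures benefit.** People with "suspected aspiration (i.e., EAT-10 score > 2" are excluded, so scores may drift upward afterwards. A higher score is worse, and the drift acts in both arms. It makes within-arm change hard to read but does not by itself bias the contrast between arms.

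It can also be said that covariates are commonly left to a full analysis plan. That would excuse silence. Here the tests are named, and for the secondary endpoints the named tests do not use t0. Finally, if recruitment after allocation makes expected baselines differ, adjusted and change-score analyses can estimate different things, and the variance ratios above no longer tell the whole story. That stands as a caution, but it does not rescue the raw comparisons.

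**Conclusion.** The point holds for the exploratory secondary endpoints, and for the primary only as a gain in precision. The within-arm tests do not address the randomised question and would give a pattern favouring the intervention in about 16 to 25% of trials in which both arms change equally by 0.2 to 0.45 SD. The raw between-arm tests have about 1.1 to 5.3 times the variance of adjusted ones and take in part of any baseline gap. For TTSC, adjustment would cut the variance by about 5% (ρ = 0.9) to 35% (ρ = 0.3).

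The size of the common change, the correlations, equal variances across visits and 40 analysed per arm are assumptions; the article gives neither a correlation nor an expected change within arms. The change is worth making because it is nearly free and needs no new data.

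**What to change.** For TTSC, RWT, EAT-10 and CAL, state that the treatment comparison is the difference between arms at t1 and at t2, adjusted for the participant's t0 score and reported with a confidence interval. Account for facility in the model and use a small-sample degrees-of-freedom correction, since only 10 to 12 facilities are randomised.

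Drop the significance tests at t0 and show baseline values by arm descriptively. Report within-arm changes descriptively too, without p-values, and state that they are not evidence of effect. Say whether the within-arm summaries cover TTSC.

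The cost is a change of analysis wording, slightly more modelling work, and one degree of freedom if the covariate enters at facility level. The sample size and the assessments stay as they are.

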### Evaluation

Various evaluation tools will be utilized at three time points (t_0_, t_1_, t_2_) to test the working hypotheses. Assessments of frailty [14, 22] and hearing ability will only be collected at t_0_, to verify the inclusion and exclusion criteria. Table 1 shows the timing of all measurements of individual diagnostic criteria.

**Table 1 Tab1:** Study overview regarding diagnostic measures and time points

time point	study period						
	enrollment	allocation	post-allocation			close-out	
	inclusion of LTC-facilities	statification randomization	pre-inter-vention (t_0_)	intervention	post-inter-vention (t_1_)	6-month follow up (t_2_)	intervention waiting group

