**Assessment**							
demografic and clinical data of the LTC-residents			X				
inclusion criteria of the LTC-residents: Clinical Frailty Scale			X				
inclusion criteria of the LTC-residents: speech audiometry			X				
*clinical assessments*							
cognitive ability: Dementia-Detection-Test (DemTect)			X		X	X	
language ability: Regensburg Word Fluency Test (RWT), semantic and phonological verbal fluency			X		X	X	
swallowing ability: Timed Test of Swallowing Capacity (TTSC)			X		X	X	
Questionnaire about every day Communication Practice– Communicative Activity Log (CAL)			X		X	X	
quality of everyday swallowing: Eating Assessment Tool (EAT-10)			X	X	X	X	X
*process evaluation*							
notes and protocols of the intervention process diary of the Residents				X			
evaluation of the intervention: feedback questionnaire for residents					X		
**intervention group**				X			
**control-waiting group**							X

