Univariate and bivariate statistical procedures, as well as multivariable regression analyses (i.e., linear and logistic), will be used to assess possible associations between different dependent and independent variables, such as the influence of the LTC facility or sex. Continuous variables will be presented as means and standard deviations, while categorical variables will be presented as median and interquartile ranges.

The process evaluation will be based on an analysis of the documented frequency or continuity of active participation in the training units, the frequency of self-training, and the survey, which will be primarily evaluated quantitatively using univariate statistical methods (e.g., frequency counts, measures of central tendency, dispersion). In addition, subgroup analyses using bivariate statistical methods are planned (e.g., examination of a connection between participation frequency or dropout rate and the presence of mild to moderate frailty or dementia). Field notes, short minutes of sessions, and free-text information in the survey will undergo content analysis and topic evaluation [24].

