### Strengths and limitations

Currently, no preventive group intervention program for swallowing and speech competence is available to older individuals in LTC facilities in Germany. Individual therapy is prescribed only in the event of a diagnosed disorder (e.g., dysphagia, aphasia), typically at significant cost to the individual. To our knowledge, no prior study has investigated the effectiveness of preventive intervention programs for swallowing and speech competence among older individuals. However, previous studies investigating group intervention programs for LTC facility residents (e.g., physiotherapeutic muscle training, cognition training) have shown positive effects for muscular deterioration (e.g., sarcopenia) [22, 25] and cognition and language [6]. Likewise, group intervention programs for the treatment of dysphagia and aphasia in LTC facilities have been positively evaluated [26].

The results of this project are expected to provide important insights into the effectiveness of preventive programs to maintain speech, language, and swallowing abilities in older individuals, which might support the establishment of care guidelines. Positive long-term effects are also expected through the participatory design and the teaching of safe swallowing and word retrieval strategies, which will enable residents to continue improving their swallowing and speech skills post-intervention.

It is possible that some limitations of the research will affect the results. In particular, recruitment poses a potential challenge, given reported high dropout rates of up to 52% in studies of LTC facility residents and dysphagic patients, more generally [27]. However, the defined inclusion and exclusion criteria aim at excluding more vulnerable individuals (i.e., with pre-existing dysphagia), thereby mitigating potential dropout due to illness or death. Nevertheless, it is possible that a high dropout will be observed due to high frailty. A significant proportion of LTC facility residents may be too frail to benefit from or participate in the proposed intervention program, as current data show that individuals tend to stay in their own home for as long as possible before moving into an LTC facility [8]. Once this move has been made, residents often require therapy, rather than preventive measures. Thus, it is possible that the target population for the proposed intervention will need to be recruited elsewhere (i.e., from senior centers, rather than LTC facilities).

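### The frailty part of the one named subgroup analysis has no eligible participants, because the inclusion criterion excludes mild or moderate frailty

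*Protocol article*

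**What the plan says.** Three statements in the protocol article bear on this point.

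- **Eligibility** (Characterization of LTC facilities as clusters and participants). A resident must have "no mild or moderate frailty (i.e., Clinical Frailty Scale: level < 5", as judged by caring professionals. On cognition, the exclusion covers "moderate or severe dementia (i.e., DemTect ≤ 8".
- **Timing** (Evaluation). Frailty and hearing assessments "will only be collected at t_0_, to verify the inclusion and exclusion criteria". Table 1 agrees: the Clinical Frailty Scale (CFS) is marked only at t0. The row "cognitive ability: Dementia-Detection-Test (DemTect" is marked at t0, t1 and t2.
- **Analysis** (Data processing and statistics, process evaluation). The text states that "subgroup analyses using bivariate statistical methods are planned" and gives one example, the "examination of a connection between participation frequency or dropout rate and the presence of mild to moderate frailty or dementia".

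The discussion (Strengths and limitations) adds that "it is possible that a high dropout will be observed due to high frailty".

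**The concern.** The frailty category used as a grouping variable is, in almost the same words, the category that the inclusion criterion removes. A comparison of attendance or dropout by presence of that frailty then has one group and no comparator. Both statements cannot be carried out as printed, so either the grouping or the inclusion wording is misstated.

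Two things are at stake. First, the article treats dropout as a real threat. It cites rates from 10 to 52%, assumes about 20%, and looks to the process evaluation for adjustments if dropout is high (Description of the study process). Its only named analysis linking frailty to dropout would return nothing. Second, the target population becomes unclear. Facilities recruit on the printed criterion, while the analysis text reads as if frailer residents could take part.

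**Working it through.** **Inputs, all from the protocol article**

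- Eligible frailty: CFS below 5, labelled as the absence of mild or moderate frailty (inclusion criteria).
- Grouping variable: presence of mild to moderate frailty or dementia (Data processing and statistics).
- Frailty measured at t0 only; DemTect at t0, t1 and t2 (Evaluation; Table 1).
- Number of participants: 12 facilities with about 8 each, or approximately 100 (Characterization of LTC facilities; Sample size calculation).

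**Step 1: the denominator.** The sample size is based on a "two-tailed unpaired t-test with a significance level set to 5% and a power of 80" per cent, with a difference of 2.8 ml/s, SD 3 ml/s, ICC 0.1 and 8 residents per cluster.

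- Individually randomised t-test: 19.03 per arm.
- Design effect: 1 + (8 − 1) × 0.1 = 1.7.
- Per arm: 19.03 × 1.7 = 32.4. Clusters: 32.4 / 8 = 4.04, rounded up to 5.
- Total: 2 × 5 × 8 = 80. With 20% dropout: 80 / 0.8 = 100.

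The article's figures reproduce. The alternative count is 12 × 8 = 96. The denominator is therefore about 96 to 100. Frailty enters none of these steps.

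**Step 2: overlap for frailty.** On the article's own labels, the eligible levels are those below 5, and mild or moderate frailty is whatever is not below 5. The two sets have no level in common, so the expected frail group is 0 of about 96 to 100. This does not depend on the exact cut-off, because the criterion also rules out the category by name. Only residents enrolled in breach of the criterion could fill the group.

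**Step 3: later reclassification.** Frailty is not measured after t0. A resident who becomes frail during follow-up is never recorded as such, so the group stays empty.

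**Step 4: overlap for dementia.** The exclusion names moderate or severe dementia and equates it with DemTect of 8 or less. On that labelling, mild dementia may be present at entry. The repeat measurements at t1 and t2 also record later decline. This part of the analysis can have members. If mild to moderate is meant to qualify dementia as well, its moderate range is excluded at entry, but the mild range is not.

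**Step 5: a combined indicator.** If frailty or dementia is meant as one yes/no variable, the analysis runs, but every member of the group enters through dementia. It would then say nothing about frailty.

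**The case against.** The strongest case on the other side is that this hardly matters. The analysis is one illustration within an exploratory process evaluation. None of the stated hypotheses depends on it, and neither the primary t-test on swallowing capacity nor the sample size uses it. Half of the example, the dementia half, can still be run. All of this stands, and it limits the weight of the point. It does not remove the contradiction: no other section resolves it, and this is the only subgroup analysis that the article names.

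A reader might infer three stronger things that the article does not support.

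- *That the discussion shows frail residents were meant to be enrolled.* The sentence is hedged: "it is possible that a high dropout will be observed due to high frailty". The text that follows is about residents of such facilities in general and about recruiting elsewhere. It is weak evidence of intent.
- *That the 20% dropout assumption fails.* The assumption appeals to the eligibility criteria as a whole, but the only feature named in support is the absence of pre-existing dysphagia. Admitting frailer residents without dysphagia would call for a fresh justification; it would not by itself refute the figure.
- *That the trial loses power.* This needs two further suppositions: that a frailer population was intended, and that its dropout reaches the top of the cited 10 to 52% range. That range comes from studies of nursing home residents with pre-existing dysphagia and of nursing home residents more generally. Neither supposition follows from the contradiction, so no power figure belongs to this point.

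**Conclusion.** The inconsistency is real but narrow. With the printed inclusion criterion and frailty measured only at t0, the frailty group in the planned analysis has 0 of about 96 to 100 participants, and that comparison cannot be carried out. The dementia comparison can be. The primary analysis and the sample size are unaffected. What suffers is one exploratory analysis and the clarity of the target population.

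The conclusion assumes that eligibility is applied as printed and that the article's own equation of CFS below 5 with no mild or moderate frailty holds. The article does not show whether the criterion or the analysis text is the one misstated. The point is minor and worth correcting because the correction is cheap.

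**What to change.** Reconcile the inclusion criterion with the process-evaluation text.

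- **If the printed eligibility stands:** replace the frailty grouping by the association of attendance and dropout with baseline CFS level, treated as ordinal within the eligible range, and with DemTect score, treated as continuous. Both are already collected at t0, so no new measurement is needed. State that the CFS result describes only the levels below 5.
- **If the inclusion wording is the error:** correct it, tell the facilities, and justify the 20% dropout assumption again for the population then described.

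The article gives no screening date. If recruitment has begun, the CFS levels recorded at t0 show which population was actually enrolled, and the report should say so. As text, either change is a matter of wording; the second would also change whom the facilities screen in, and the article requires modifications to be notified and approved in writing (Ethics).
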